# Clinical added value of MRI to CT in patients scheduled for local therapy of colorectal liver metastases (CAMINO): study protocol for an international multicentre prospective diagnostic accuracy study

**DOI:** 10.1186/s12885-021-08833-1

**Published:** 2021-10-18

**Keywords:** Colorectal cancer, Colorectal liver metastases, Liver metastases, Liver MRI, Abdominal CT scan, Diffusion weighted imaging, Gadoxetic acid, Hepatic resection, Liver surgery, Thermal ablation

## Abstract

**Background:**

Abdominal computed tomography (CT) is the standard imaging method for patients with suspected colorectal liver metastases (CRLM) in the diagnostic workup for surgery or thermal ablation. Diffusion-weighted and gadoxetic-acid-enhanced magnetic resonance imaging (MRI) of the liver is increasingly used to improve the detection rate and characterization of liver lesions. MRI is superior in detection and characterization of CRLM as compared to CT. However, it is unknown how MRI actually impacts patient management. The primary aim of the CAMINO study is to evaluate whether MRI has sufficient clinical added value to be routinely added to CT in the staging of CRLM. The secondary objective is to identify subgroups who benefit the most from additional MRI.

**Methods:**

In this international multicentre prospective incremental diagnostic accuracy study, 298 patients with primary or recurrent CRLM scheduled for curative liver resection or thermal ablation based on CT staging will be enrolled from 17 centres across the Netherlands, Belgium, Norway, and Italy. All study participants will undergo CT and diffusion-weighted and gadoxetic-acid enhanced MRI prior to local therapy. The local multidisciplinary team will provide two local therapy plans: first, based on CT-staging and second, based on both CT and MRI. The primary outcome measure is the proportion of clinically significant CRLM (CS-CRLM) detected by MRI not visible on CT. CS-CRLM are defined as liver lesions leading to a change in local therapeutical management. If MRI detects new CRLM in segments which would have been resected in the original operative plan, these are not considered CS-CRLM. It is hypothesized that MRI will lead to the detection of CS-CRLM in ≥10% of patients which is considered the minimal clinically important difference. Furthermore, a prediction model will be developed using multivariable logistic regression modelling to evaluate the predictive value of patient, tumor and procedural variables on finding CS-CRLM on MRI.

**Discussion:**

The CAMINO study will clarify the clinical added value of MRI to CT in patients with CRLM scheduled for local therapy. This study will provide the evidence required for the implementation of additional MRI in the routine work-up of patients with primary and recurrent CRLM for local therapy.

**Trial registration:**

The CAMINO study was registered in the Netherlands National Trial Register under number NL8039 on September 20th 2019.

**Supplementary Information:**

The online version contains supplementary material available at 10.1186/s12885-021-08833-1.

## Background

Colorectal cancer is the third most common cancer and the second most common cause of cancer related death worldwide [1]. Approximately 30% of patients with colorectal cancer present with colorectal liver metastases (CRLM) or will develop CRLM during follow-up [2–4]. Surgery is the cornerstone of curative intent therapy for these patients with 5-year survival exceeding 40% [3, 5, 6]. In recent years, local ablative techniques are increasingly performed to treat small CRLM showing comparable long-term outcomes to surgical resection in these selected patients [7–11]. Both surgery as well as thermal ablation require accurate detection of CRLM. Therefore, optimal pre-interventional localization of CRLM is of utmost importance to determine an adequate local therapy plan.

The current routine diagnostic workup of patients with suspected CRLM consists of contrast-enhanced computed tomography (CT) [12–14]. While CT provides adequate whole-body staging and has a sensitivity of 70–90% for CRLM lesions of more than 10 mm, the reported sensitivity of CT in the detection of small CRLM (≤10 mm) ranges from 22 to 68% [15–17]. This suggests that CT might not be the optimal diagnostic tool to characterize small liver lesions. In recent years, magnetic resonance imaging (MRI) and positron emission tomography CT with fluorine 18 fluorodeoxyglucose (FDG-PET-CT) have been used in addition to CT to increase accuracy [18–20]. Previous studies reported a lower sensitivity (74.1% vs. 82.1%) of FDG-PET-CT and a higher specificity (93.9% vs. 73.5%) as compared to CT [21]. A recent multicentre randomized trial demonstrated that FDG-PET-CT resulted in a modest change in surgical management of only 8.7%, not meeting the predefined minimum incremental diagnostic accuracy of 25% in that study, without an effect on overall survival [22].

Liver MRI is increasingly used as an additional imaging modality for staging of CRLM since it is considered to be more accurate for detection of CRLM as compared to CT [23–26]. To improve the performance of liver MRI, several different contrast agents have been developed, such as Gadoxetic acid (Primovist™, Bayer Schering Pharma, Berlin, Germany). Gadoxetic acid is a liver-specific MR contrast agent that has both dynamic and hepatocyte-specific properties, improving detection and characterization of focal liver lesions [27]. For the detection of CRLM, a gadolinium contrast-enhanced MRI scan has a sensitivity and specificity of 90 and 87%, respectively, while the reported sensitivity and specificity of gadoxetic acid contrast-enhanced MRI is 87–100 and 95%, respectively [24, 28]. Furthermore, MRI with diffusion-weighted imaging (DWI) in addition to gadoxetic acid enhanced MRI may substantially increase the accuracy of detection of focal liver lesions and reduce overdiagnosis of CRLM [29–31].

Although previous literature suggests that liver MRI is superior in detection and characterization of CRLM compared to CT, it is not known whether the higher diagnostic accuracy of MRI has sufficient impact on patient management in terms of additional clinically significant CRLM (CS-CRLM) that actually change the local therapy plan. The current European Society for Medical Oncology (ESMO) consensus guideline for the management of patients with metastatic colorectal cancer recommends the use of MRI in the pre-interventional workup of CRLM, but indicates that more evidence is needed to address the clinical added value of MRI in patients with CRLM [14]. In addition, the American College of Radiology (ACR) Appropriateness Criteria—Pretreatment Staging of Colorectal Cancer highlighted the difficulty to determine the best imaging modality for patients with CRLM because very few studies have adequately compared the accuracy of MRI to high-quality CT [13]. Since the available evidence supports that both MRI and CT detect liver lesions with high accuracy, the ACR Appropriateness Criteria state that CT or MRI may be used to stage CRLM [13]. These inconclusive guideline recommendations stress the lack of robust data and thorough scientific evidence in this field. Hence, the actual role of liver MRI for management of patients with CRLM remains unclear. Until now, no definitive evidence has been provided on the impact of liver MRI on finding CS-CRLM as compared to CT for patients with primary or recurrent CRLM.

The aim of the present CAMINO study is to evaluate whether diffusion-weighted and gadoxetic acid enhanced liver MRI has sufficient clinical added value to CT in order to be routinely performed in the staging of CRLM. This is an international multicentre prospective diagnostic accuracy study assessing the proportion of patients with CRLM scheduled for local therapy in which liver MRI finds additional CS-CRLM as compared to CT. The hypothesis is that the higher accuracy of liver MRI will lead to finding of at least 10% additional CS-CRLM compared to CT, resulting in improved decision-making on the local therapy plan, such as additional surgery or ablation and potentially preventing unnecessary surgical exploration or ablative treatment. The secondary aim of this study is to identify subgroups which benefit most from additional liver MRI.

## Design/methods

### Study design

The CAMINO study is an international multicentre prospective incremental diagnostic accuracy study on the added value of liver MRI including DWI and gadoxetic acid enhanced T1-weighted sequence in patients with CRLM who are considered candidates for local therapy based on CT. Patients will be recruited in 17 liver surgery centres in the Netherlands, Belgium, Norway and Italy: Amsterdam UMC, Amsterdam; Erasmus University Medical Center, Rotterdam; Leiden University Medical Center, Leiden; University Medical Center Groningen, Groningen; Netherlands Cancer Institute, Amsterdam; OLVG, Amsterdam; Amphia Hospital, Breda; Medical Spectrum Twente, Enschede; Jeroen Bosch Hospital, ‘s Hertogenbosch; St. Antonius Hospital, Nieuwegein; Maxima Medical Center, Veldhoven; IJsselland Hospital, Capelle aan den IJssel; Albert Schweitzer Hospital, Dordrecht (all in the Netherlands); Oslo University Hospital, Oslo, Norway; AZ Groeninge, Kortrijk, Belgium; Hospital Oost-Limburg, Genk, Belgium and Poliambulanza Foundation Hospital, Brescia, Italy. Due to the large number of participating centres, a phased implementation of the start of the study will be used.

All participating centres have a formal multidisciplinary team (MDT) meeting at least once per week for patients with CRLM and all have extensive experience in the diagnostic workup and in both liver surgery and thermal ablation, defined as performing ≥20 procedures annually. Treating surgeons and interventional radiologists are board certified and have performed and/or supervised at least 100 procedures.

The study is formally endorsed by the Dutch Colorectal Cancer Group (DCCG), the Abdominal Radiology section of the Radiological Society of the Netherlands (NVvR) and the Dutch Colorectal Patient Foundation (Stichting Darmkanker). The study is funded by the Dutch Cancer Foundation (KWF Kankerbestrijding) and co-funded by Bayer Schering Pharma® (Berlin, Germany) in terms of providing Gadoxetic acid for all patients. The Dutch Cancer Foundation and Bayer Schering Pharma® (Berlin, Germany) had no role in the design of the study and will not have any influence on the collection of data, data analysis, interpretation of data, writing of manuscript, and decision to publish. The study is registered in the Netherlands National Trial Register (NL8039, September 20th 2019).

This study will be conducted in accordance with the guidelines of Good Clinical Practice and in agreement with the Declaration of Helsinki (64th version, October 2013). The Medical Ethical Review Board (METc) of the Amsterdam UMC, location AMC, has assessed primarily that the CAMINO study was NOT subject to the Medical Research Involving Human Subjects Act (WMO). The METc of every participating hospital supported the decision of the METc of the Amsterdam UMC, location AMC and approved their participation in this study by signing a non-interventional study agreement. For designing this study protocol, the SPIRIT 2013 and STARD 2015 recommendations were used [32, 33] (SPIRIT Checklist provided in Additional file 1).

### Objectives and hypotheses

The main objective of this study in patients with CRLM is to identify the proportion of patients in which liver MRI including DWI and gadoxetic acid enhanced T1-weighted sequence finds CS-CRLM in addition to an abdominal portal venous phase CT. CS-CRLM are defined as liver lesions that have not been incorporated in the initial resection and/or ablation plan based on CT, hence leading to a change in local therapy. Change in local therapy is defined as any change in surgery or thermal ablation including increase or decrease of the number or extent of liver resections, increase or decrease in number of ablation zones, surgery to ablation, ablation to surgery, addition of ablation to surgery and cancellation of local therapy. The local therapy plan proposed by the MDT based on CT only will be compared to the local therapy plan based on CT and liver MRI. It is hypothesized that liver MRI will lead to the detection of CS-CRLM in at least 10% of patients which is considered the minimal clinically important difference. The findings of this study – whether or not liver MRI including DWI and gadoxetic acid enhanced T1-weighted sequence has clinical added value on local therapy strategy of CRLM patients – will determine the role of liver MRI in the staging of CRLM and will provide international guidelines with data for a scientifically based recommendation on the implementation of liver MRI in the pre-interventional workup.

The secondary aim is to identify which subgroups benefit most from the additional liver MRI by performing a logistic regression analysis and developing a clinical prediction model.

### Study population

Consecutive adult patients with primary or recurrent CRLM who are considered candidates for curative surgery, thermal ablation or a combination of curative surgery and intra-operative ablation, based on abdominal CT will be invited to the study. Patients who receive neoadjuvant or induction chemotherapy and are subsequently eligible for local curative therapy will be invited as well.

#### Inclusion criteria

To be included, patients must fulfil all of the following criteria:
Histological proof of primary colorectal cancerAge ≥ 18 years.Patients with primary or recurrent CRLM who are considered candidates for curative surgery, thermal ablation or a combination of curative surgery and intra-operative thermal ablation, determined during MDT based on abdominal CT.Written informed consent.

#### Exclusion criteria

Patients fulfilling one or more of the following criteria will be excluded:
Contraindications for liver surgery or thermal ablation.Extrahepatic metastases on CT-chest/abdomen and no realistic option for curative therapy.Unresectable primary tumor, or resectable primary tumor requiring immediate surgery.Patients with contra-indications for liver MRI.Previous inclusion in the CAMINO study.

### Informed consent

Informed consent will be obtained for the use of individual patient data for study purposes. The formal written informed consent will be obtained during the outpatient clinic visit by a member of the study team. By signing the informed consent form, patients agree to participate in this study. Before patients agree to participate in this study, they will be provided with written information in the form of a Patient Information Sheet. All patients will be informed about the strict confidentiality of their patient data, and that their medical records may be reviewed for study purposes by authorized individuals other than their treating physician. Participants will be told that they may withdraw from the study at any time for any reason. This will not have any influence on subsequent care. Patients who do not want to participate in the study will have the current routine preoperative workup. Patients withdrawing permission will be replaced.

Liver MRI is a non-invasive imaging method used in daily clinical practice and under intensive quality control as part of its clinical applications. Safety reporting and a data safety monitory board (DSMB) are therefore not implemented in this study as there are no added risks.

### Study procedures

#### Preoperative imaging

In this study, all participants will undergo both abdominal CT and liver MRI. An abdominal CT will include a contrast-enhanced CT scan using a portal venous phase protocol. Liver MRI includes at least T2-weighted sequence, T1-weighted sequence with gadoxetic acid as contrast agent (i.e. plain, arterial, portal venous, early delayed and late delayed phase) as previous studies showed that gadoxetic acid has become the preferred contrast agent in liver MRI for CRLM, and DWI [24, 30]. Since gadoxetic acid will be administered immediately before the start of MRI, the duration of the scan will not exceed the standard duration with any other contrast agent. In every participating centre there is substantial experience with the use of gadoxetic acid and also with interpretation and assessment of gadoxetic acid enhanced liver MRI.

Both CT and liver MRI will be performed according to the imaging protocols from the Radiological Society of the Netherlands (Additional file 2). These protocols give guidance and are considered as minimal requirements for scanning in all participating centres. Prior to the start of the study, the protocol per scanner is retrieved from each study site and checked to see whether it meets the minimum requirements concerning type of scanner, dose of iodinated contrast, scan delay, kilovoltage dose, collimation and slice thickness for CT and magnetic field strength, type of contrast agent, dose of contrast agent, scan series, scan sequences and b values for DWI for MRI. Patients referred from other centres to the participating center with prior CT (and MRI) are also eligible. Imaging from those referral centres can be used, but only when it meets the protocol requirements of the Radiological Society of the Netherlands. If the abdominal radiologist from the participating center deems that imaging quality does not meet protocol requirements, imaging has to be repeated.

All pre-interventional imaging will be assessed by an experienced abdominal radiologist. Liver MRI will be assessed by a radiologist who is not blinded to CT results since liver MRI is performed in addition to CT in daily clinical practice. The radiologist has access to information about previous CT results and the interpretation of the liver MRI may be influenced by this additional information. However, we aim to evaluate the clinical added value of liver MRI in addition to CT and this reflects how both examinations are used in daily clinical practice.

The aim is to perform all preoperative examinations within a window of 6 weeks prior to the day of surgery and/or ablation, with an extension possible to a maximum of 10 weeks. The time interval between CT and liver MRI is 4 weeks at maximum. This time interval for CT and MRI is based on the rapid growth potential of CRLM and the importance of CT and MRI being performed within a sufficiently short time interval while taking into account the feasibility of arranging liver MRI in participating centres.

If there are contraindications for gadoxetic acid, liver MRI is performed with another routinely used extracellular contrast medium at the participating center or –when contraindicated– no contrast medium is used. A small subset of patients may undergo FDG-PET-CT instead of CT. These patients are also eligible to participate. However, we will perform a subgroup analysis excluding patients that underwent FDG-PET-CT.

#### Multidisciplinary team meeting

In all participating centres, potentially eligible patients will be discussed during a formal regular MDT meeting (Fig. 1). First, the CT will be presented by the radiologist and indication for local therapy will be determined by the MDT. If a patient is considered candidate for local therapy, the exact surgical or ablative plan based on CT only will be decided and documented in the electronic case report form (eCRF). After finalizing and documenting the CT-based local therapy plan, the findings of liver MRI are disclosed as a second step. This will be either – if directly available – at the same MDT meeting, or at the next MDT meeting, after liver MRI has been performed (no longer than 4 weeks after CT). CS-CRLM found at liver MRI with the exact change in the local therapy plan will be documented in the eCRF. CS-CRLM are defined as liver metastases that have not been incorporated in the initially planned resection or ablation based on CT, therefore leading to a change in local therapeutical management. Change in local therapy plan is defined as any change in surgery or thermal ablation including increase or decrease of the number or extent of liver resections, increase or decrease in number of ablation zones, surgery to ablation, ablation to surgery, addition of ablation and cancellation of local therapy.

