### Expert panel procedure and evaluation

In addition to the primary outcome measure which will be determined in the daily clinical workflow of the participating centres, a fixed central independent, blinded expert panel is created to validate the findings of the individual centres as a secondary outcome measure. The expert panel consists of three abdominal radiologists, two interventional radiologists and three liver surgeons. These are recruited from participating centres and will post-hoc evaluate step-by-step the additional value of liver MRI as compared to CT only on the local therapy plan. The participating radiologists have extensive experience with CT and liver MRI and have assessed at least 500 abdominal CT scans and 500 liver MRI scans for focal liver lesions. The participating liver surgeons performed at least 100 liver resections. The participating interventional radiologists have extensive experience in performing thermal ablation of CRLM and performed at least 100 liver ablation procedures. The CT and liver MRI of each patient will be assessed by one radiologist only since all radiologists have extensive experience in assessing abdominal CT scans for focal liver lesions and liver MRI scans. Radiologists will not review examinations from their own centre. Based on CT and liver MRI findings of the radiologist, each interventional radiologist and surgeon will get the findings presented and will indicate independently whether they would change their initial local therapeutical plan based on the liver MRI results. Agreement of 4/5 expert panel members (agreement rate of 80% or more) will be considered as consensus. In case of agreement of three or less expert panel members, a joint consensus meeting will be organized to discuss the respective cases and eventually reach consensus.

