## Discussion

It is unknown to what extent liver MRI may result in a change in clinical management in patients with CRLM scheduled for local therapy based on staging with CT. Current evidence is based on single centre retrospective studies. The present international multicentre prospective study will determine the clinical added value of liver MRI to CT in patients with CRLM scheduled for local curative therapy including liver resection and/or thermal ablation.

A non-randomized design was chosen since a randomized controlled trial comparing abdominal CT and liver MRI versus CT was considered not feasible due to the high use of MRI in current daily practice. A retrospective analysis to document the incremental value of liver MRI compared to CT is not reliable, since a regular MDT meeting structure does not include a consistent step-by-step documentation of the added value of MRI on final patient management.

In contrast, it is also important to acknowledge the burden of performing an additional liver MRI in the workup of patients with CRLM. Performing routine liver MRI in all CRLM patients may add diagnostic delay due to waiting lists and limited MRI-capacity. Indeterminate lesions at liver MRI could make it more difficult to decide on an accurate surgical or ablative strategy. In addition, CT in combination with surgical exploration and IOUS is considered as the standard for CRLM detection and is performed in all patients, questioning the added value of liver MRI and its associated costs. As adding routine liver MRI to the workup of CRLM patients may cause additional pre-interventional delays and increases healthcare costs, any recommendation about its use should be guided by high quality studies which determine its exact added value.

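### The radiologist who presents the CT may already know the MRI when the CT-only plan is made, and the own-centre bar on the expert panel does not clearly reach its five voters

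*Protocol article*

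**What the plan says.** Under Study outcomes, the Protocol article takes the primary outcome from a comparison of the team's CT-only plan with its plan after CT and MRI.

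Under Multidisciplinary team meeting it sets the order: "First, the CT will be presented by the radiologist and indication for local therapy will be determined by the MDT". The exact plan is entered in the eCRF, and then: "After finalizing and documenting the CT-based local therapy plan, the findings of liver MRI are disclosed as a second step". That second step may come "at the same MDT meeting, or at the next MDT meeting, after liver MRI has been performed"; the same-meeting route applies when the MRI is directly available.

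Under Preoperative imaging, an MRI may exist before the first meeting: "Patients referred from other centres to the participating center with prior CT (and MRI) are also eligible". On readers it says: "All pre-interventional imaging will be assessed by an experienced abdominal radiologist". It then explains why the MRI reader is not blinded to the CT.

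Under Expert panel procedure and evaluation, a central panel described as independent and blinded validates the local findings as a secondary outcome. It has three abdominal radiologists, two interventional radiologists and three liver surgeons, all from centres taking part. The own-centre rule is: "Radiologists will not review examinations from their own centre". For the vote, "each interventional radiologist and surgeon will get the findings presented and will indicate independently" whether the MRI would change their plan. Four of five (80% or more) is consensus; three or fewer leads to a joint meeting.

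**The concern.** The CT-only plan is the comparator for the primary outcome, so it should reflect what the CT alone would have led to. The article controls the order in which the team hears the findings. It does not control what the person presenting the CT already knows. A presenter who has read the MRI may point out a faint CT lesion that would otherwise have been missed, and the MRI then adds less. The same presenter may leave an equivocal CT lesion for the MRI to settle, and the MRI then adds more.

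The panel is the planned check on the local result. If a voter took part in the patient's care or in the local meeting, that vote is not fully independent of the result being checked.

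**Working it through.** **Part 1: the CT-only plan.** The article gives no figure for this point, so the check is mainly a reading of the sections against each other.

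- *Can an MRI exist and have been read before the CT-only plan is made?* Yes. The same-meeting route presupposes that the MRI is available, and referred patients may arrive with one.
- *Must the CT presenter be unaware of it?* No such rule is stated. CT and MRI are not required to have different readers.
- *Does the stated justification cover this?* No. It covers an MRI reader who knows the CT, which mirrors practice when MRI is added to CT. The reverse, a CT presenter who knows the MRI, affects the baseline.
- *Would the per-protocol analysis remove these patients?* No. The same-meeting route is permitted, so it is not a deviation. The three named subgroup analyses (preoperative chemotherapy, FDG-PET-CT, number of metastases) do not divide patients this way either.

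Illustration of size. The 10% is the postulated proportion in the sample size section. Two inputs are assumed: f, the share of patients whose CT presenter knew the MRI, and k, the relative shift in yield among them. The observed proportion is 10% × (1 ± f × k).

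| f | k | f × k | Observed proportion |
|---|---|---|---|
| 0.10 | 0.10 | 0.01 | 9.9% to 10.1% |
| 0.25 | 0.25 | 0.0625 | 9.4% to 10.6% |
| 0.50 | 0.20 | 0.10 | 9.0% to 11.0% |
| 0.50 | 0.50 | 0.25 | 7.5% to 12.5% |

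In the third row the shift is 1 percentage point, about 3 of 298 patients (0.01 × 298 = 2.98). For scale, the article's stated lower confidence bound of 6.5% lies 3.5 points below 10%.

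**Part 2: the panel.**

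- Voters: 3 surgeons + 2 interventional radiologists = 5, which matches the four-of-five rule.
- Ceiling on patients with an own-centre voter, if the five come from five different centres of the 17 and enrolment is equal: 5/17 = 0.294, and 0.294 × 298 ≈ 88 patients.
- If the bar on radiologists is read to include interventional radiologists, three surgeons remain: 3/17 = 0.176, about 53 patients.
- If all five voters came from one centre: 1/17 = 0.059, about 18 patients.

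**The case against.** The main safeguard is in the text: the CT-only plan must be decided and documented before the MRI is disclosed. That stands. The gap is limited to the presenter's prior knowledge, in patients whose MRI was read before that plan was made.

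Three stronger readings are tempting, and the documents support none of them.

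- *That the bias lowers the primary proportion.* Foreknowledge can act either way, and nothing in the article settles which effect dominates.
- *That a large share of patients is affected.* The Discussion says a randomised trial was not feasible "due to the high use of MRI in current daily practice". That describes how often MRI is used, not how often it is read before the CT-only plan is made.
- *That patients whose MRI rules out local therapy are lost before consent.* Consent is placed at the outpatient visit, with no statement that this follows MRI disclosure. Recruitment is consecutive, eligibility rests on CT, cancellation counts as a change of plan, and follow-up is provided for such patients.

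A further objection is that sensitivity analyses belong in an analysis plan or full protocol, neither of which is shown, and that the meeting flowchart is missing from the text at hand. That is fair: the absence of a sensitivity analysis from the article is not itself the fault. The point rests on what the article does state, namely the same-meeting route, the eligibility of patients with prior MRI, and a justification that covers one direction only.

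On the panel, voters do not read scans. They receive findings from a radiologist of another centre, the data are coded by study number, and one vote among five has limited weight. All of this lowers the risk. It does not stop a surgeon from recognising a patient he or she treated or discussed, and the article does not say what the panel is blinded to.

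**Conclusion.** The point holds in a limited form. The article permits the CT-only plan to be presented by a radiologist who already knows the MRI, and its reasoning on blinding does not cover that case. The primary proportion can be biased in either direction by an unknown amount. The range shown, from 9.9%–10.1% to 7.5%–12.5% around a true 10%, rests wholly on assumed shares and shifts and is not an estimate of the actual bias.

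The panel's own-centre bar does not clearly extend to its five voters. This affects a secondary outcome only. The 29% is a ceiling that needs voters from five different centres and equal enrolment, neither of which is stated.

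Neither part invalidates the design. Both can be put right cheaply, and the first matters more because it bears on the primary outcome.

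**What to change.** 1. Record in the eCRF whether the MRI had been acquired, and whether it had been read, when the CT-only plan was documented. Add a sensitivity analysis of the primary proportion restricted to patients whose CT-only plan was documented before the MRI was read.
2. Extend the own-centre bar to every voting panel member and apply the existing 80% rule to those who remain. After one recusal this means 4 of 4, since 3 of 4 is 75%; otherwise the case goes to the existing consensus meeting.

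The cost is one or two eCRF fields, one extra analysis and a few more cases for the consensus meeting. The restricted analysis is less precise. If half of 298 patients (149) qualified and 10% had the outcome, the one-sided 95% Wald lower bound would be 0.10 − 1.645 × √(0.09/149) = 6.0%, against 0.10 − 1.645 × √(0.09/298) = 7.1% in the full set. The restricted patients may also differ in case mix, for instance by containing fewer referrals, so a difference from the main result would be a signal to examine and not proof of bias.
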